### Safety and monitoring

#### Withdrawal

Participants can withdraw their consent for involvement in the study at any time, without an obligation to justify the decision and without consequences for their usual care. The research team can advise withdrawing participants from the intervention if it is deemed to be in the best interest of the participant. Participants who withdraw from the study are not replaced. The Data Safety and Monitoring Board (DSMB) can advise to stop the study.

#### (Serious) adverse events

To avoid prolonged periods of thyroid hormone under-replacement potentially resulting in symptoms of hypothyroidism, levothyroxine treatment is discontinued gradually while monitoring thyroid function after each reduction. Within the ThyPRO-39, symptoms of hypothyroidism are assessed as a possible adverse effect. All adverse events (including cardiovascular events) reported spontaneously by the participant or their GP are recorded and followed up. If complaints are reported during the discontinuation phase, these will be assessed by the research nurse. It is at the discretion of the GP to decide to either continue the withdrawal of levothyroxine or to maintain or increase the dosage. Serious adverse events are sought out actively and reported to the sponsor, the accredited Medical Ethics Committee (MEC), and competent authority using electronic case report forms.

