#### Discontinuation phase

The discontinuation phase starts with baseline measurements of thyroid function and secondary outcome parameters (see table 1), followed by a consultation of the participant with their GP during which discontinuation of levothyroxine is initiated, except when TSH level ≥10 mU/L. Levothyroxine is discontinued stepwise, and at intervals of ≥6 weeks to ascertain a steady-state concentration has been reached before the following control visit. This is in line with standard clinical practice. During each ‘6 week’ visit, the GP evaluates thyroid function and symptoms with the participant. On agreement, the daily dose of levothyroxine can then be lowered provided thyroid function is within the predefined limits, that is, a normal fT4 and TSH <10 mU/L. With each step, the dose of levothyroxine is reduced by approximately 25 mcg (the use of whole tablets is preferred) until a daily dose of 25 mcg or less is reached. The GP is free to adjust the size of the dose reduction if necessary. The maximum dose reduction in medication is 50 mcg in the first step. In the final step, the medication is discontinued completely if the laboratory results are still within the predefined limits. The discontinuation phase ends after the evaluation of complete withdrawal of the levothyroxine treatment (ie, 6 weeks after the final discontinuation step). Secondary outcome parameters are collected at the first ‘6 week’ visit and the end of discontinuation (see table 1).

Participants are requested to stop the discontinuation phase when a TSH level ≥10 mU/L or an fT4 level below the normal range is identified during a control visit and is confirmed by an extra thyroid function measurement within 2 weeks. When the extra measurement does not confirm a TSH level ≥10 mU/L or a low fT4 level, the participant is allowed to proceed with the discontinuation phase. Factors other than thyroid function, such as symptoms, may however be a reason to prematurely stop the discontinuation or restart levothyroxine. On stopping the discontinuation phase, it is at the discretion of the physician and the participant to decide whether the dose of levothyroxine at that moment will be maintained or increased. Participants who have stopped the discontinuation phase prematurely will be followed up in accordance with the protocol if possible.

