### Descriptive study data and outcome measures

Descriptive data recorded at prebaseline include (see online supplemental appendix 2):

10.1136/bmjopen-2022-070741.supp2Supplementary data

Age and sex.Lifestyle: smoking, alcohol intake.Medical history.Complex health problems (Integrated Systematic Care for Older Persons (ISCOPE) questionnaire).^27 28^The participant’s attitude towards deprescribing (revised Patients’ Attitudes Towards Deprescribing (rPATD) questionnaire).^29^Treatment satisfaction for levothyroxine treatment (Treatment Satisfaction Questionnaire for Medication (TSQM)).^30^The participant’s view on what is a substantial dose reduction of levothyroxine (Goal Attainment Score (GAS)).

The primary outcome is the proportion of participants who withdraw their thyroid medication successfully (defined as normal fT4 levels and TSH levels <10 mU/L) at 52 weeks after the start of the discontinuation (final follow-up).

Secondary outcome measures determined at baseline and/or final follow-up include (see online supplemental appendix 2):

Thyroid-related quality of life (ThyPRO-39).^31 32^General health-related quality of life (EuroQol-5D, including the EuroQol visual analogue scale.^33^ Cognitive function is determined as an additional dimension (EuroQol-5D+C).^34 35^Participant’s view on whether they achieved a substantial dose reduction of levothyroxine (Goal Attainment Scale (GAS)).Participant’s view on regret after the decision to withdraw levothyroxine (Decision Regret Scale (DRS)).^36^

To further explore the quality of life during the discontinuation phase, ThyPRO-39 and EuroQol measurements were also determined 6 weeks after the first step of lowering the dose of levothyroxine (T6) and 6 weeks after the last step of dose-lowering (see table 1).

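### Non-serious adverse events are collected by spontaneous report under contact that differs by phase, so their counts cannot be compared across the phases of this self-controlled trial

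*Protocol article*

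**What the plan says.** The section (Serious) adverse events sets two collection rules. For adverse events in general: "All adverse events (including cardiovascular events) reported spontaneously by the participant or their GP are recorded and followed up". For serious ones: "Serious adverse events are sought out actively and reported to the sponsor". It adds that "If complaints are reported during the discontinuation phase, these will be assessed by the research nurse" and leaves it to the GP whether withdrawal then goes on. It names one structured symptom measure: "Within the ThyPRO-39, symptoms of hypothyroidism are assessed as a possible adverse effect".

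The section Discontinuation phase has the GP look at symptoms throughout the taper: "During each ‘6 week’ visit, the GP evaluates thyroid function and symptoms with the participant". On questionnaires it says: "Secondary outcome parameters are collected at the first ‘6 week’ visit and the end of discontinuation". Table 1 also schedules ThyPRO-39 at weeks -12, 0 and 52.

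The section Study phases and interventions gives a 12-week control phase, a discontinuation phase of 6 to 36 weeks, and follow-up from its end (Tx) to week 52. Table 1 shows no visit between Tx and week 52.

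**The concern.** The trial has no control group. Study design says that outcomes are compared within participants, and the Introduction hypothesises that a considerable share of older users can stop without being worse off. A within-person comparison of harm needs events to be found in the same way in each period.

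For non-serious events this is not so. Collection is passive, and the opportunities to report differ by phase: two contacts at the ends of the control phase, frequent visits in the taper, then a long interval with none. Nurse assessment of complaints is stated for the taper alone. Followed as written, the plan could yield more non-serious events in the taper because participants are seen more often, and fewer afterwards because they are not seen. A statement about tolerability that rests on those counts would have no like-for-like reference.

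**Working it through.** **1. Collection rule by type of event**

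| What is collected | How | Phases stated |
|---|---|---|
| Serious adverse events | sought actively | no limit stated |
| Other adverse events, including cardiovascular | spontaneous report by participant or GP | no limit stated |
| Complaints assessed by the research nurse | when reported | discontinuation phase |
| GP symptom review | at each 6-week visit | discontinuation phase |
| ThyPRO-39 | questionnaire | weeks -12, 0, 6, Tx, 52 |

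The article does not say that symptoms found at the GP review are entered as adverse events. The GP may report them, but no step requires it.

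**2. Length of each phase**

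Inputs: steps of about 25 mcg, intervals of 6 weeks (the stated minimum) and a dose limit of 150 mcg, all from Study population and Discontinuation phase. For a taper of n steps:

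- Tx = 6n weeks. A 25 mcg starter has n = 1, so Tx = 6. A 150 mcg starter has n = 150/25 = 6, so Tx = 36. This reproduces the article's range of 6 to 36 weeks.
- Interval from Tx to week 52 = 52 - 6n.
- Share of the 52 weeks = (52 - 6n)/52.

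| Starting dose (mcg) | n | Tx (week) | Tx to week 52 (weeks) | Share | Step controls without ThyPRO-39 |
|---|---|---|---|---|---|
| 25 | 1 | 6 | 46 | 88% | none |
| 50 | 2 | 12 | 40 | 77% | none |
| 75 | 3 | 18 | 34 | 65% | week 12 |
| 100 | 4 | 24 | 28 | 54% | weeks 12, 18 |
| 125 | 5 | 30 | 22 | 42% | weeks 12, 18, 24 |
| 150 | 6 | 36 | 16 | 31% | weeks 12, 18, 24, 30 |

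A first step of 50 mcg, the largest that the article allows, removes one step for starting doses of 50 mcg and above. A 150 mcg starter then has Tx = 30, a follow-up interval of 22 weeks, and no ThyPRO-39 at weeks 12, 18 and 24.

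**3. Interval between scheduled contacts**

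- Control phase: 12 weeks.
- Taper: about 6 weeks.
- Follow-up: 16 to 46 weeks.

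Relative to the taper, the interval is 12/6 = 2 times as long in the control phase and 16/6 = 2.7 to 46/6 = 7.7 times as long in follow-up. The research nurse's contacts described under Adherence come before each measurement or when data are missing. Their stated purpose is data quality and retention, so they follow the same timetable and do not fill the follow-up gap.

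**4. What ThyPRO-39 covers**

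In a completed withdrawal it is taken twice before the taper (weeks -12 and 0), after the first step (week 6), 6 weeks after the last step (Tx, at zero dose) and at week 52. Week 6 and Tx coincide in a one-step taper. The Data analysis plan compares measurements before and after discontinuation. The questionnaire is absent only at intermediate step controls, where the GP reviews symptoms and thyroid function.

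**The case against.** The strongest reply has four parts.

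- **The aims measure harm by other means.** The secondary aims turn absence of harm into thyroid-related quality of life, general health and the participant's view of the decision. All but the last have control-phase values. The article plans no comparison of non-serious event rates between phases. This stands, and it limits the point to what the event counts can be used for.
- **The GP is a stated route into the adverse event record.** Symptoms found at a 6-week visit can reach it that way. This stands as a possibility, but it depends on the GP choosing to report, and it exists only in the taper.
- **The nurse sentence may describe taper management.** It leads directly to the GP's decision on whether to go on, so it need not limit event collection. That is fair: the word only is not in the text, and spontaneous reports are recorded in every phase. What remains is that no equivalent assessment is stated for the other phases.
- **An article condenses the full protocol.** This would answer a complaint about missing detail. Spontaneous reporting, however, is a rule that the article states and sets beside active search for serious events.

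A reader might infer more than the article supports:

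- *ThyPRO-39 skips weeks 12 to 30.* The last-step column in Table 1 runs over weeks 6 to 36. All four intermediate controls lack it only in a six-step taper.
- *Symptoms are missed at the lowest dose, or cannot be compared with the control phase.* ThyPRO-39 is taken at zero dose at Tx and week 52 in completed withdrawals, and it has two values before the taper.
- *The taper is unobserved.* The GP reviews symptoms and thyroid function at each visit.
- *The Data Safety and Monitoring Board sees a distorted picture.* Serious events are sought actively and reported immediately, and the board also receives periodic reports.
- *Harm is under-counted overall.* More frequent taper visits may equally raise counts relative to the control phase, so the net direction is not known.

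**Conclusion.** The point holds in limited form. Non-serious adverse events, including non-serious cardiovascular events, are collected passively. Scheduled contact is about 6-weekly in the taper, 12 weeks apart in the control phase, and absent for 46 down to 16 weeks after Tx (88% to 31% of the 52 weeks). Their counts therefore cannot be compared across phases, and they would not support a claim that stopping is well tolerated. Serious events and thyroid-related symptoms are better protected.

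This is a weakness of design, not a contradiction in the text. The week counts assume steps of about 25 mcg, intervals of exactly 6 weeks and completed withdrawal. Longer intervals would shorten the follow-up gap, and a larger first step would lengthen it. The number of events missed cannot be estimated from the article. The change is worth making because it is cheap and uses visits that already take place.

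**What to change.** Amend the section (Serious) adverse events as follows:

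1. Enter symptoms and events found at the GP's existing 6-week review in the visit form as adverse events.
2. Ask the same short, fixed event question, including cardiovascular events, at weeks -12, 0, Tx and 52. At weeks 0 and 52 it covers the whole interval since the last contact.
3. Apply the same assessment of reported complaints in the control, taper and follow-up phases.
4. Report non-serious events per person-week separately for the three phases, and state that contact frequency differed. Use each participant's actual time in each phase, since the article lets participants with suppressed TSH start discontinuation at once.

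The cost is a few fields in the existing electronic data capture system, slightly more nurse work in follow-up, and more minor events on record. A single question at week 52 still relies on recall over up to 46 weeks, so step 4 needs its caveat. Extra ThyPRO-39 administrations at intermediate controls are optional and not part of the fix. No dose, schedule or stopping rule changes.

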#### Monitoring

At regular intervals, the DSMB advises the study project group and sponsor (Leiden University Medical Center (LUMC)) whether it is safe and appropriate to continue the study. Periodic routine reports on the progress of the study are sent to the DSMB for review. Serious adverse events are reported immediately. No interim analyses for efficacy or futility will be performed. The DSMB meets at least five times and is composed of medical experts and a biostatistician without any involvement in the study as investigators or as study participant care physicians. The DSMB members are professor [name] (Chair; Department of Cardiology, LUMC), [name] (Department of Internal Medicine—Endocrinology, LUMC) and [name]. [name] (Department of Biomedical Data Sciences, LUMC).

Annual study monitoring visits are conducted by an independent clinical research associate (LUMC) according to a study-specific monitoring plan.

A summary of the study progress is submitted to the MEC yearly, including the date of inclusion of the first participant, the number of participants included, the number of participants that have completed the trial, serious adverse events and amendments.

Roles and responsibilities (committees) are also described in online supplemental appendix 3, as is additional trial information regarding trial registration data and trial sponsor.

10.1136/bmjopen-2022-070741.supp3Supplementary data

### Patient and public involvement statement

An online survey (July 2017) revealed that 92% of Dutch GP practices find that investigating the effects of levothyroxine treatment discontinuation is relevant to primary care. The Older People Advisory Board Health and Well-being has carefully reviewed the research proposal and their comments were used for improvement. In a letter of recommendation, the Older People Advisory Board Health and Well-being has given its full support and endorsement. The results will be discussed with the Older People Advisory Board Health and Well-being as well.

## Ethics and dissemination

This study will be conducted according to the principles of the Declaration of Helsinki (amended most recently in October 2013), in accordance with the Dutch Medical Research Involving Human Subjects Act (WMO), the Guideline for Good Clinical Practice (May 1996) and in full conformity to any applicable state or local regulations. In accordance with Dutch legal requirements (WMO), participants will be insured by an insurance of the LUMC to provide cover for damage to research participants through injury or death caused by the study (see online supplemental appendix 1). The protocol has been approved by the accredited MEC (Medisch Ethische Toetsingscommissie Leiden-Den Haag-Delft). Any protocol modifications will be communicated to all relevant parties (including the accredited MEC, the DSMB, participating GPs, participants and trial register).

To comply with the general social responsibility associated with clinical research, the study results will be proactively disseminated to the general public and key public health stakeholders including Schildklier Organisatie Nederland, the patient advocacy group. The findings will be submitted for peer-reviewed publication in national and international medical journals. Publications will be approved by the principle investigators. Individual deidentified participant data can be shared on request only, when the participant has given permission (ie, informed consent) for data sharing concerning future research regarding thyroid disease and treatment with levothyroxine. The study protocol and the statistical analysis plan will be made available online before publication of the main results from this study.
